## Methods/Design

### Subjects

Patients with post-acute ankle sprains will be recruited to participate in this study from multiple clinical centers across the United States. The Institutional Review Boards of the University of the Pacific (Stockton, CA, USA) and Des Moines University (Des Moines, IA, USA) approved this study protocol. This study protocol is registered with http://www.clinicaltrials.gov (NCT00888498).

Inclusion criteria for this study are age 16-60 years, onset of ankle sprain at least 2 weeks prior to enrollment, and Foot and Ankle Ability Measure Activities of Daily Living (FAAM ADL) subscale score less than or equal to 67 points (ie, respondent indicates ≥20% disability). Exclusion criteria involve current assisted ambulation (eg, cane or crutches); inability to bear weight through the affected extremity immediately after injury with tenderness to palpation of the medial and lateral malleolar zones, styloid process of the 5^th ^metatarsal, and navicular [36]; positive anterior drawer or inversion stress maneuver suggesting ligamentous laxity [37-39]; volume of the affected limb greater than 10% of the unaffected limb per water displacement volumetry [40]; previous history of ligament or bony reconstructive surgery to the ankle and foot; concomitant injury to other lower extremity joints; and inability to comply with the treatment protocol.

A total of 189 subjects will be recruited (n = 63 per group). A group size of 52 subjects will provide 80% statistical power to detect an 8-point (9.5%) difference in FAAM ADL subscale score based on Martin and colleagues' data[41], with additional subjects recruited to account for a 20% dropout rate [42]. This sample size ensures the study is powered to detect a statistically and clinically significant difference between groups using a 2-sample t-test (Figure 1).

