**Figure 1 F1:**
[figure not shown]
**Group size vs. effect size plot given d = .4 (arrow), β ≥ .80, and α = .05 for a 2-sample t-test**. Optimal sample size occurs at n = 52 per group. Adding an additional 20% to group size to account for potential drop-outs, group size for this study was estimated at n = 63.

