### Data Analysis

The primary dependent variable for this study is FAAM score at 1 week, 4 weeks, 6 months, 1 year, and 2 years. Secondary dependent variables include NPRS, modified FABQ, PANAS, LExSES, and GROC scores at 1 week, 4 weeks, 6 months, 1 year, and 2 years. The independent variable is the manual therapy intervention condition. All other outcome measures will be assessed as potential covariates of treatment success, which is defined as the achievement of minimum clinically important change score on the FAAM for this study.

Descriptive statistics will be calculated for the data set, including frequencies, means, and standard deviations. Between and within-group comparisons will be made for outcome measurements at 4 weeks, 6 months, 1 year, and 2 years post-enrolment. Analysis of variance with appropriate post-hoc pairwise comparisons will be used to assess between-groups differences for continuous data. Statistical significance of between-group differences in categorical data will be assessed with chi square analysis. Pearson correlations and multivariate linear regression analyses will be performed to determine statistical significance of associations with treatment success and failure. An intention-to-treat analysis will be performed for subjects who drop out of the study after enrolment but prior to completion of all study procedures. Statistical significance of inferential statistical tests will be accepted at α≤.05.

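### The printed sample-size inputs cannot all hold: with d = 0.4, 52 per group gives about 52% power (two-sided), not 80%, and 63 per group does not preserve 52 after 20% dropout

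*Protocol article*

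**What the plan says.** The sample-size justification is in two places in the protocol article.

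- **Subjects section:** "A group size of 52 subjects will provide 80% statistical power to detect an 8-point (9.5%) difference in FAAM ADL subscale score". The section attributes the 8 points to a cited study of the instrument, sets recruitment at 189 (63 per group) to allow for 20% dropout, names a between-group 2-sample t-test, and says this size makes certain that the study is powered for a statistically and clinically significant difference.
- **Figure 1 caption:** "Group size vs. effect size plot given d = .4 (arrow), β ≥ .80, and α = .05 for a 2-sample t-test". The value .80 is labelled β but evidently means power. The caption calls 52 per group optimal and goes on: "Adding an additional 20% to group size to account for potential drop-outs, group size for this study was estimated at n = 63".

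Neither place states an SD or whether the test is one- or two-sided. The Data Analysis section adds only the significance level: "Statistical significance of inferential statistical tests will be accepted at α≤.05".

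**The concern.** A 2-sample t-test at alpha 0.05 with a standardised difference of 0.4 needs far more than 52 per group for 80% power, so at least one of the printed figures must be wrong. The dropout step also looks wrong, because adding 20% to a target does not offset losing 20% of those enrolled.

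Eight points is the change that the article's description of the FAAM gives as the minimum clinically important one for the ADL subscale. The power claim therefore governs how a non-significant result will be read. If d = 0.4 is right, a true 8-point difference would be missed about half the time, and a null result could be taken as evidence against a benefit that the trial was poorly placed to detect. If d = 0.4 is a misprint, the design may be close to what is claimed, but the article gives no means of telling.

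**Working it through.** **Inputs**

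| Input | Value | Source |
|---|---|---|
| Difference | 8 points | Subjects |
| Standardised difference d | 0.4 | Figure 1 caption |
| Alpha | 0.05, sidedness not stated | Figure 1 caption, Data Analysis |
| Power | 80% | Subjects, Figure 1 caption |
| Test | 2-sample t-test between groups | Subjects, Figure 1 caption |
| n per group | 52, raised to 63 | Subjects, Figure 1 caption |
| Dropout | 20% | Subjects |
| SD | not stated; 8/0.4 = 20 if d = 0.4 is right | derived |

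**1. Attempt to reproduce 52 per group.** The normal approximation is n = 2(z_alpha + z_power)²/d².

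- Two-sided: 2 × (1.960 + 0.842)²/0.16 = 98.1, so 99. The exact noncentral t gives 99.08, so 100.
- One-sided: 2 × (1.645 + 0.842)²/0.16 = 77.3, so 78. The exact t gives 77.97, so 78.

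Neither gives 52.

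**2. Power at the stated n.** The noncentrality is d × √(n/2) = 0.4 × √26 = 2.04 with 102 degrees of freedom, against a two-sided critical value of 1.98.

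| n per group | Two-sided power, d = 0.4 | One-sided power, d = 0.4 |
|---|---|---|
| 50.4 (63 less 20%) | 51.1% | 63.7% |
| 52 | 52.4% | 64.8% |
| 63 (no dropout) | 60.6% | 72.2% |

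No sidedness gives 80%, even if nobody drops out.

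**3. What would make 52 per group correct.** Solving for d at 80% power and n = 52 gives d = 0.555 two-sided, so SD = 8/0.555 = 14.4. One-sided, d = 0.491 and SD = 8/0.491 = 16.3. For 8 points with 52 per group, two-sided:

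| Assumed SD | d = 8/SD | Power |
|---|---|---|
| 12 | 0.667 | 92% |
| 14 | 0.571 | 82% |
| 16 | 0.500 | 71% |
| 20 | 0.400 | 52% |

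**4. Dropout step.** The caption's step is 52 × 1.2 = 62.4, so 63; this reproduces the stated figure. But 63 × 0.8 = 50.4, which is below 52. Keeping 52 after 20% dropout needs 52/0.8 = 65 per group, or 195 in total against the planned 189.

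**5. Detectable difference after dropout, if d = 0.4 (SD 20) stands.** At 50 per group, 80% power two-sided requires d = 0.566, and 0.566 × 20 = 11.3 points.

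**The case against.** The strongest objection is that no SD is printed. The value 20 comes from dividing 8 by the printed d, so it holds only if that d is the correct figure. The 8 points are tied to a cited study that is not available here, and an SD of about 14.4 or less would make 52 per group adequate two-sided. This stands. A reader might infer that the trial simply has about 52% power for its clinically important difference; the article does not establish that. It establishes that d = 0.4, n = 52, 80% power and a 2-sample t-test are not all true.

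Two other inferences are tempting and should not be drawn. One is that 52 was taken from a different calculation, such as a paired t-test. More than one calculation yields 52, and the article does not say how it was obtained. The other is that power falls further because three groups are compared. The Data Analysis section says only that "Analysis of variance with appropriate post-hoc pairwise comparisons will be used to assess between-groups differences for continuous data". It names no correction, and sizing a three-arm trial on one pairwise comparison is common, so no adjusted figure can be attributed to the plan.

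It can also be said that the dropout slip is small, and that an intention-to-treat analysis is planned for subjects who drop out. The first is true: the shortfall is about two per group and moves power at d = 0.4 only from 52.4% to 51.1%. The second does not rescue the step, because the article's own allowance treats dropouts as lost to the calculation.

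That an article condenses a fuller protocol is no answer. This is a numerical claim printed with its inputs, and it does not follow from them.

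**Conclusion.** The sample-size statement is wrong as written and must be corrected. On the printed inputs, the stated n is about half of what is required (52 against 100 two-sided; 78 one-sided), and the stated power of 80% compares with 52% (65% one-sided). This contradiction does not depend on the unknown SD.

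Which figure is wrong does depend on it. With an SD of about 14.4 or less, the two-sided claim for 8 points at 52 per group holds and d = 0.4 is the error. With an SD of 20, d = 0.4 is consistent with 8 points and the 80% claim is the error. The two-sided figures assume an unadjusted comparison of two groups at alpha 0.05.

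The dropout error is separate, minor and certain: 63 enrolled leaves 50.4, not 52.

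**What to change.** In the Subjects section and the Figure 1 caption:

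1. State the SD taken from the cited data and the sidedness of the test.
2. Reconcile d with the 8-point difference, and label .80 as power rather than β.
3. Correct the dropout step: say that 63 enrolled with 20% dropout leaves about 50 per group, and that keeping 52 would have needed 65.
4. Recompute and restate the power for 8 points, or the detectable difference, at about 50 per group.

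If the SD proves to be 20, the restated text is about 51% power for 8 points and 80% power for about 11.3 points (two-sided, without adjustment for multiple comparisons). In that case, also remove the description of 52 per group as optimal and the assurance that the size secures power for a clinically significant difference.

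The cost is wording only. The correction itself requires no extra enrolment, although the stated power may become less favourable.

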### Experimental groups

Subjects will be randomized into 3 groups after pre-participation screening is completed, informed consent is obtained, and baseline measures are recorded (Figure 2). The first group (n = 63) will receive talocrural traction manipulation (Figure 3). With the subject in a seated position on a treatment table and the lower extremity of interest stabilized to the table with a belt, the standardized treating therapist will grasp the foot of interest with the thenar eminences on the foot's plantar surface. A thrust will be delivered parallel to the long axis of the subject's lower leg after the treating therapist induces passive ankle dorsiflexion to end range. The second group (n = 63) will receive talocrural traction mobilization. Traction will be delivered to the talocrural joint at the treating therapist's second perception of tissue resistance in 3 bouts of 30-second holds, separated by 10 seconds of rest. The third group (n = 63) will receive the manual therapy control intervention. This will consist of the same patient and clinician preparation for the mobilization/manipulation techniques. However, the treating therapist will maintain passive DF ROM for the duration of 1 deep inhalation and exhalation by the subject. Following the procedure, all subjects will receive range of motion exercises involving 10 clockwise ankle and foot circles within a symptom-free range of motion. Subjects will be requested to complete this exercise 4 times daily for 10 repetitions each session.

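### The sample size is for one two-group t-test, but the planned analysis is a three-group ANOVA with post-hoc pairwise comparisons, so the stated 80% power does not carry over to a pairwise result unless the pairs are left unadjusted

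*Protocol article*

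**What the plan says.** The Subjects section of the protocol article bases the group size on a single comparison of two groups. It states "A group size of 52 subjects will provide 80% statistical power" for an 8-point difference in FAAM ADL score and adds: "This sample size ensures the study is powered to detect a statistically and clinically significant difference between groups using a 2-sample t-test (Figure 1". The Figure 1 legend gives the inputs as "given d = .4 (arrow), β ≥ .80, and α = .05 for a 2-sample t-test". The group size is then raised from 52 to 63 for 20% dropout, 189 subjects in all.

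The design and analysis differ from this. Under Experimental groups: "Subjects will be randomized into 3 groups after pre-participation screening is completed". Under Data Analysis: "Analysis of variance with appropriate post-hoc pairwise comparisons will be used to assess between-groups differences for continuous data", with the significance level given as "Statistical significance of inferential statistical tests will be accepted at α≤.05". The post-hoc procedure is not named. Neither the SD nor the sidedness of the test is given.

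**The concern.** The power claim belongs to one t-test at the full .05. The trial's questions are which of manipulation, mobilization and hands-on placebo differ from one another, and in the planned analysis the post-hoc comparisons answer them. Most post-hoc procedures either raise the critical value for a pair or require a significant overall F first, and both lower the power for that pair.

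If pairwise power is nearer two-thirds than four-fifths, a true 8-point effect is missed about one time in three rather than one in five. Eight points is also the minimum clinically important change that the article gives for the ADL subscale. A reader who trusts the stated 80% could take a non-significant pair as evidence that no clinically important effect exists.

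**Working it through.** **Inputs from the article.** n = 52 evaluable and 63 recruited per group; difference 8 points; power 80% (the legend's β ≥ .80 is read as power); α = .05; d = .4; 20% dropout.

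**Assumed.** Two-sided testing, equal SDs, equal group sizes.

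**Step 1: reproduce the stated figure.** Power of a two-sample t-test is P(|T| > t(.975, 2n − 2)), where T is noncentral t with noncentrality d√(n/2). With d = .4 and n = 52 the noncentrality is 0.4 × √26 = 2.04 and power is 52% (65% one-sided). For 80%, d = .4 needs 99-100 per group, or 78 one-sided. The stated 80% therefore does not follow from the printed d, and d = .4 with 8 points implies SD = 8/0.4 = 20.

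**Step 2: grant the stated 80%.** To isolate the effect of the three-group analysis, solve for the d that gives exactly 80% at n = 52, two-sided .05. The result is d = 0.555, so SD = 8/0.555 = 14.4. Neither figure is in the article.

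**Step 3: power for one pair in the three-group analysis.** The pooled error has 3 × 52 − 3 = 153 df, and the noncentrality is 0.555 × √26 = 2.83. Critical values for |t|:

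- unadjusted: t(.975, 153) = 1.976
- Tukey: q(.95; 3, 153)/√2 = 2.367
- Bonferroni, three pairs: t(1 − .05/6, 153) = 2.421

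F-protected LSD (overall F significant and |t| > 1.976) was simulated. The lower figure has the third group midway between the other two; the upper figure has it equal to one of them. Dunnett covers only the two comparisons with placebo, and its critical value was simulated.

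| Procedure | n = 50, d = 0.555 | n = 52, d = 0.555 | n = 63, d = 0.555 | n = 52, d = .4 |
|---|---|---|---|---|
| Unadjusted | 79% | 80% | 87% | 53% |
| F-protected LSD | 68-74% | 70-76% | 79-84% | 40-45% |
| Dunnett (2 comparisons) | 71% | 72% | 81% | 43% |
| Tukey | 66% | 68% | 77% | 37% |
| Bonferroni (3 pairs) | 64% | 66% | 76% | 35% |

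The n = 50 column is what remains after the planned loss: 63 × 0.8 = 50.4.

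**Step 4: related figures at n = 52, d = 0.555.** The overall F has 71% power with the third group midway and 83% with two groups equal, but it does not say which pair differs. With Tukey, 80% power is reached at d = 0.630, that is 0.630 × 14.42 = 9.1 points.

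**Step 5: the price of no adjustment.** If three unadjusted pairwise tests are run and no group differs, the chance of at least one false-positive pair at a given time point is about 12%.

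**The case against.** **The 66-68% range depends on two choices that the article does not make.** A reader might infer that power is 66-68% even with every sample-size input accepted. It is not: those figures set aside the printed d = .4 and use a back-solved d of 0.555. With d = .4 accepted, the plain t-test already has only 52% and Tukey 37%. A reader might also infer that the plan commits to a three-pair adjustment or an overall F gate. The Data Analysis section says only that the post-hoc comparisons will be appropriate. Protected LSD is a legitimate choice for three groups and gives 70-76%; unadjusted tests keep 80%. Both points stand, so the result has to be given as a range with its assumptions.

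**The analysed number may be larger than 52.** An intention-to-treat analysis is planned. If all 63 per group contributed full information, protected LSD would give 79-84% and Dunnett 81%, and the shortfall would largely disappear; Tukey would still be at 77%. This stands as the favourable limit. It is not the article's own planning case, which allows for 20% loss and makes its claim at 52.

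**An unnamed post-hoc procedure is a detail for the analysis plan.** Agreed; its absence here is not the fault. The fault is that the article states both a sizing test and an analysis, and the two differ.

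**Sizing a multi-arm trial on one pair is common and is openly stated.** This is fair as a convention. But the sentence in the Subjects section says that the study is powered for differences between groups, and that does not follow for the analysis described later.

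**A three-group ANOVA with f = 0.25 needs about 52 per group.** This may be coincidence. The article states d = .4 and a two-sample t-test, and such a calculation would power the overall F, not the pairs.

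**Conclusion.** The mismatch is real: a two-group t-test at the full .05 sizes a three-group trial analysed by ANOVA with post-hoc pairs, and no allowance is made for three comparisons.

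Granting the stated 80% at 52 per group, every error-controlling procedure computed falls short for an 8-point pair, by about 4 points (80 − 76, protected LSD at best) to 14 points (80 − 66, Bonferroni). This rests on two-sided testing and on an SD of about 14.4 that has no source in the article. If the printed d = .4 is kept, power is far lower under any procedure, mainly because d = .4 does not yield 52 per group; that is a separate defect, to be settled first.

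The documents do not support a single figure of 66-68% as the trial's power. Nor does this point show that the trial must enrol more subjects. It shows that the stated power is not that of the planned analysis, unless the pairs are tested unadjusted at about 12% familywise error per time point.

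**What to change.** 1. In the Subjects section and the Figure 1 legend, first reconcile d, the SD, the 8-point difference and 52 per group, giving the SD and its source and whether the test is two-sided. No multiplicity-adjusted power can be stated reliably before this is done, and the back-solved SD of 14.4 should not be written in as if it were sourced.
2. Then replace the two-sample t-test claim with the power of the pairwise procedure that will be used under Data Analysis, or with the difference that it can detect with 80% power. As an illustration, if the SD proved to be 14.4, Tukey at 52 per group would detect about 9.1 points.
3. If unadjusted pairwise tests are intended, say so and give the familywise error beside the 80%.

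Enrolment and procedures are unchanged. The only cost is a less favourable stated power.

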**Figure 1 F1:**
[figure not shown]
**Group size vs. effect size plot given d = .4 (arrow), β ≥ .80, and α = .05 for a 2-sample t-test**. Optimal sample size occurs at n = 52 per group. Adding an additional 20% to group size to account for potential drop-outs, group size for this study was estimated at n = 63.

### Pre-Participation Screening Measures

#### Foot and Ankle Ability Measure (FAAM)

The FAAM is a self-report questionnaire consisting of a 21-item ADL subscale and 8-item Sports subscale, in addition to a global rating of self-perceived foot function from 0-100% [41]. This inventory demonstrates satisfactory internal consistency, validity, and score stability. Test-retest validity is satisfactory for use in research designs involving repeated measures (ICC_2,1 _= .87-.89). Minimum clinically important change scores have been identified for the ADL subscale (8 points) and Sports subscale (9 points) with respect to patient global rating of change.

#### Anterior drawer test

The anterior drawer test is a manual assessment of the integrity of the anterior talofibular ligament (ATFL) [43]. It is performed with the patient in supine hook-lying position to relax the plantaflexor muscle group, and the ankle of interest plantarflexed 10-15 degrees [44]. The evaluating therapist stabilizes the tibia and fibula while translating the calcaneus and talus anteriorly. A positive test involves the perception of excessive movement by the investigator or the appearance skin dimpling on the anterolateral ankle [45]. This test demonstrates diagnostic specificity to detect rupture of the ATFL, and as little as 2 mm of excessive excursion may be detected manually [37,39].

#### Inversion stress maneuver

The inversion stress test is intended to elicit symptoms or excessive mobility due to calcaneofibular ligament rupture [38]. It is performed with the subject in supine. The evaluating therapist stabilizes the affected leg, and moves the calcaneus into inversion and adduction, with the foot positioned neutrally in the sagittal plane.

#### Volumetric measurement of the foot, ankle, and lower leg

Water displacement volumetry will be used to assess for the presence of clinically significant ankle edema, which is operationally defined as ≤10% difference in left and right limb volume in this study. In this test, the subject will first place their uninvolved foot in a 32.5 × 12.5 × 22.5 cm clear acrylic box containing a known volume of water. As the subject's foot enters the box, water will flow from a spout in a box into a graduated cylinder. Measurement of displaced water will be completed and then the displaced water will be discarded. The graduated cylinder will be dried thoroughly and replaced beneath the box spout. The subject will then place their involved foot into the box, and the volume of displaced water will be measured. This volume represents the difference in volumes between involved and uninvolved sides. The residual volume of water displaced by the involved side will then be divided by the volume of water displaced by the uninvolved side. Water displacement volumetry demonstrates strong intra-tester reliability (ICC_2,1_=.99) and inter-tester reliability (ICC_2,1_=.93-.97) [46,47]. The 10% inter-limb difference criteria adopted for this study exceeds the margin of diurnal variability in water displacement measurements [40].

